### Trial development

The trial has been designed in line with the SPIRIT guidelines [54] in a project group consisting of the following key stakeholders: Occupational therapists with experience of treating patients with CMC1-OA, researchers with expertise in HOA, and a patient research partner with experience from living with HOA, including having undergone CMC1-surgery and receiving non-pharmacological interventions. Members of the project group will be engaged throughout each stage of the trial and will contribute in the process of integrating study results in clinical practice.

### Study design and setting

This is a Norwegian multicentre randomized controlled trial (Trial registration: NCT01794754). The trial will be conducted at the departments of rheumatology at St. Olav’s Hospital, Trondheim University Hospital in Trondheim, Haukeland University Hospital in Bergen and Haugesund Rheumatism Hospital in Haugesund, in collaboration with the National advisory unit on rehabilitation in rheumatology, which is located at Diakonhjemmet Hospital in Oslo. Participants will be allocated to receive either standard care (no intervention) or occupational therapy during the waiting period between referral for and the actual surgical consultation (see Fig. 1). The occupational therapy intervention represents a supplement to standard HOA care, and no participant will receive an intervention that is below the current standard of care.

**Fig. 1 Fig1:**
[figure not shown]
Study flow diagram

### Participants

All persons who are referred by their GP for surgical consultation due to their CMC1-OA at one of the three participating departments of rheumatology are eligible for the RCT. However, persons who do not speak the Norwegian language will be excluded, as will those with cognitive dysfunction or with other diseases or injuries that may negatively impact hand function. The local project coordinator at each centre will have access to lists of patients who are referred for surgical consultation and will mail written information about the study to potential participants. The local project coordinator will telephone those who agree to participate and will book them for the next convenient appointment for the baseline assessment, which is expected to last approximately one hour. A questionnaire will be sent to the participant, who will be encouraged to fill it out and bring it to the appointment. On arrival at the centre, the local project coordinator will screen the potential participant for eligibility before discussing the study with participants and obtaining their written informed consent prior to further assessment and randomization.

Those who do not respond to the mailed written information or who fail to appear at the appointment for baseline assessment will not be re-contacted regarding participation in the study.

### Data collection

Participant flow is shown in Fig. 1. Follow-up will be at 4 months (immediately before the surgical consultation), 18 months and 24 months after randomization to evaluate short, medium and long-term effects. Before each follow-up, a questionnaire will be sent to the participants, who will be asked to fill it in at home and bring it to the follow-up appointment.

Additionally, participants in the control group will receive a phone call 2 weeks after baseline assessments, and will complete the MAP-Hand in a telephone interview. Participants in the intervention group will be convened for a second consultation 2 weeks after baseline, at which time the orthoses and the hand exercise programme will be adjusted, and additional information regarding use of assistive devices will be given if needed.

The surgical consultation takes place immediately after the follow-up assessment at 4 months. Based on the patient’s symptoms, functional limitations and degree of CMC1-OA, the surgeon may reach one of the three following conclusions;the patient is not eligible for surgery, and will need a new referral from his/her GP to be scheduled for a new surgical consultationthe patient is scheduled for a new surgical consultation after 6 to 12 months, due to uncertainty related to eligibility, orthe patient is eligible for surgery and will receive an appointment for operation, (usually after 6 to 10 months on a waiting list).

All participants who are operated on, regardless of group affiliation, will be given post-operative treatment according to surgical procedures and recommendations.

The third and fourth follow-up will be after 18 and 24 months, respectively. Baseline assessments will be repeated, and for participants in the occupational therapy group, exercises and orthoses will be adjusted if needed. Participants in the control group will receive the occupational therapy intervention after assessments at the control at 24 months.

Each participant will have a special numeric code, and all data will be stored in a fireproof and locked cupboard and in a digital file on the research server at Diakonhjemmet Hospital. Selected members of the project group (project leader, local coordinators, bio-statistician, study assistants, a PhD-student and a post doc research fellow) can access the file. The OT will check missing data in the questionnaires at each follow-up. An independent study assistant will check incorrect and double data entries.

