### Randomization and allocation concealment

The randomization schedule will be prepared by a biostatistician making a computer-generated, randomized list with a block size of 10.

A secretary will prepare sealed, opaque envelopes containing the patient’s assignment to either the occupational therapy or the control group. The envelopes will be stored in a locked closet at each centre and may be opened by the participant after baseline assessments and information about HOA are completed.

In this trial, participants and therapists delivering the intervention are aware of the treatment assigned. To achieve blinding in the surgical consultation, participants will be asked not to inform the surgeon about their group allocation during the consultation. Moreover, the statistician who will perform the main statistical analyses will be blinded to group allocation.

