### Intervention providers

Six occupational therapists (two at each centre) with at least 4 years of experience within rheumatology will provide the occupational therapy intervention. Before the start of the inclusion process, the therapists will meet together with the project leader and the patient research partner and go through assessment and treatment procedures to ensure that these are performed and delivered consistently. Meetings will be held regularly throughout the trial period. Additionally, the project leader will answer therapists’ questions by mail or telephone between meetings.

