### Outcome measures

The primary outcome will be the number of participants in each group who have received surgical treatment after 2 years.

Secondary and tertiary study outcomes are documented in Table 4 and are based on previously validated measures.

**Table 4 Tab4:** Secondary and tertiary outcome measures

	Data collection instrument and scale	Time points
Secondary outcome measures:		
Activity performance	MAP-Hand, mean of 18 standardized and up to five patient specific activities, respectively, rating scale 1–4, 1 is no problems	t1, t2*, t3, t4, t5
Physical function and symptoms in the arm, shoulder and hand	Quick-Dash, sum-score range 1–100, 1 = good function	t1, t3, t4, t5
Current situation with regards to main reason for wanting surgery	Numeric rating scale: 0–10, 0 is as bad as could be	t1, t3, t4, t5
Pain at rest	Numeric rating scale: 0–10, 0 is no pain. Both hands.	t1, t3, t4, t5
Grip strength	In Newton by the Grippit; maximum, mean and last of 20 recordings over a 10 s interval, both hands	t1, t3, t4, t5
Pain following measure of grip strength	Numeric rating scale: 0–10, 0 is no pain, both hands	t1, t3, t4, t5
Tertiary outcomes:		
Current pain in thumb selected for surgery	Numeric rating scale: 0–10, 0 is no pain	t1, t3, t4, t5
Painful finger joints	Examination by a trained OT of presence of pain yes/no in CMC1, MCP, PIP and DIP-joints in both hands	t1, t3, t4, t5
Finger flexion	Flexion deficit in millimetre of the II, III, IV and V finger of both hands	t1, t3, t4, t5
Range of motion thumb MCP	In degrees by a goniometer, both hands	t1, t3, t4, t5
Range of motion thumb IP	In degrees by a goniometer, both hands	t1, t3, t4, t5
Palmar abduction thumb	In degrees by a pollexograph, both hands	t1, t3, t4, t5
Abduction CMC1	In degrees by a pollexograph, both hands	t1, t3, t4, t5
Pinch strength	In Newton by the Grippit; maximum, mean and last of 20 recordings over a 10 s interval, both hands	t1, t3, t4, t5
Pain following measure of pinch strength	Numeric rating scale: 0–10, 0 is no pain, both hands	t1, t3, t4, t5
Pain following exercising	Exercise diary, numeric rating scale: 0–10, 0 is no pain	t3
Satisfaction with HOA care at current centre	Numeric rating scale: 0–10, 0 is very dissatisfied	t3, t4, t5

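### No masked assessor is described for the eight observer-measured outcomes, and the text indicates that the allocation-aware therapists who give the intervention also measure them

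*Protocol article*

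**What the plan says.** All of the following is in the Methods/Design part of the protocol article.

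- **Who treats.** Intervention providers: "Six occupational therapists (two at each centre) with at least 4 years of experience within rheumatology will provide the occupational therapy intervention". Before inclusion starts, these therapists meet with the project leader and the patient research partner to "go through assessment and treatment procedures to ensure that these are performed and delivered consistently".
- **Who knows the allocation.** Randomization and allocation concealment: "In this trial, participants and therapists delivering the intervention are aware of the treatment assigned".
- **Who is masked.** The same section makes two provisions. For the surgeon: "To achieve blinding in the surgical consultation, participants will be asked not to inform the surgeon about their group allocation during the consultation". The statistician who runs the main analyses is also to be blinded. No outcome assessor is mentioned.
- **What happens at follow-up.** Data collection, on 18 and 24 months: "Baseline assessments will be repeated, and for participants in the occupational therapy group, exercises and orthoses will be adjusted if needed". The same section adds: "The OT will check missing data in the questionnaires at each follow-up".
- **Who measures.** Table 4 names an assessor for one row, painful finger joints: "Examination by a trained OT of presence of pain yes/no in CMC1, MCP, PIP and DIP-joints in both hands". The text after Table 4 lists the observer-reported measures at baseline, 4, 18 and 24 months, and then gives the therapists the further task of recording the time spent on treatment.

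**The concern.** The eight observer-measured outcomes depend in varying degree on the person taking them. Yes/no joint pain, goniometer and pollexograph angles, and flexion deficit in millimetres require handling and judgement. Grip and pinch strength are read from an electronic instrument, but they depend on maximal effort and so on instruction and encouragement. Pain after grip and after pinch is rated by the participant in connection with a test that the assessor conducts.

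If the assessor knows the group and also delivers the tested treatment, measurement after baseline can differ between the arms. The Statistical analyses section estimates between-group mean differences with confidence intervals for these outcomes at each follow-up, adjusted for baseline. Neither intention-to-treat analysis, nor baseline adjustment, nor a blinded statistician can remove a difference that arises in the measurement itself. The Discussion would make the intervention mandatory before surgery is considered if it proves effective, so the functional results that support that conclusion need to be credible.

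**Working it through.** The plan gives no figure for assessor bias, so there is none to reproduce. The check is a count and a comparison of sections.

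**Count of Table 4, matched to the list of observer-reported measures in the text**

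| Tier | Rows | Observer-measured | Self-reported |
|---|---|---|---|
| Secondary | 6 | 1: grip strength | 5: MAP-Hand, Quick-Dash, current situation for the main reason for surgery, pain at rest, pain after grip test |
| Tertiary | 11 | 7: painful joints, finger flexion, thumb MCP and IP range of motion, palmar abduction, CMC1 abduction, pinch strength | 4: current thumb pain, pain after pinch test, pain after exercising, satisfaction with care |
| Total | 17 | 1 + 7 = 8 | 5 + 4 = 9 |

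8/17 = 47% of the secondary and tertiary outcomes. By tier it is 1 of 6 secondary and 7 of 11 tertiary. Two of the nine self-reported outcomes, pain after grip and pain after pinch, are tied to a test conducted by the assessor.

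**Are provider and assessor the same people?**

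1. The six providers are prepared together for assessment as well as treatment (Intervention providers). That would have little purpose if they did not assess.
2. The one assessor that Table 4 names is an occupational therapist.
3. The paragraph on observer-reported measures moves directly to what the therapists record in addition, which ties them to those measures.
4. An occupational therapist handles the questionnaires at every follow-up (Data collection).
5. No section describes an assessor from outside this group.

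Together these support the inference that allocation-aware therapists take the measurements. They do not show that each participant is measured by his or her own therapist, because each centre has two.

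**Does treatment contact fall at the assessment visits?**

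For 18 and 24 months, yes: assessment and adjustment are given in one sentence. For 4 months the Data collection section mentions no adjustment. However, treatment time is recorded at 4 months too, Table 1 asks participants to bring the diary to their next therapy appointment, and Table 5 collects the diary data at 4 months. Only the intervention arm has a diary, so its presence alone would reveal the group to an assessor who did not already know it.

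**The case against.** The strongest reply is that the overlap is inferred. The sentence on repeating the assessments is passive and names nobody. Table 4 names an occupational therapist for one row, and the other seven observer-measured rows give only an instrument or a unit. The article is condensed, the flow diagram is not available here, and a full protocol might say who assesses whom. This stands as a limit on certainty. It does not remove the point: the article states its blinding arrangements explicitly, and they stop at the surgeon and the statistician.

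Four stronger readings are tempting, and the documents do not support them.

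- *The trial's main result is affected.* The primary outcome is receipt of surgery by 2 years, which the therapists do not measure. Seven of the eight outcomes at issue are tertiary.
- *The treating therapist reviews participants' answers on pain, function and satisfaction.* The forms are to be filled in at home, and the check is for missing data. At most, blank items might be completed in the therapist's presence.
- *Bias towards occupational therapy is present at every follow-up.* The direction is plausible, not shown. Adjustment at the same follow-up is stated only for 18 and 24 months.
- *The bias can be put as a percentage of grip strength.* Nothing in the documents supplies such a figure.

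It can also be said that using the second therapist masks only in part. Both therapists at a centre are providers and may know the allocation, participants know their own group, and the nine self-reported outcomes stay exposed under any assessor scheme. All of this is correct. It limits what the change can achieve, but the change would still separate the person who treated the participant from the person who measures.

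**Conclusion.** The point holds as a risk in the design. The passages indicate that therapists who provide the intervention and know the allocation also take the follow-up measurements, and no separate or masked assessor is described. The outcomes at risk are the eight observer-measured ones: grip strength among the secondary outcomes and seven tertiary ones. The pain ratings after grip and pinch testing may be affected as well. The risk is least in the reading of grip and pinch, which is electronic, and greater where the assessor judges an angle, a distance or the presence of pain.

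The conclusion rests on reading several sections together and on the assumption that no document outside this article names an independent assessor. The size of any bias is unknown. The sample size and the primary analysis are unaffected. The change is worth making because it is cheap and protects the functional results.

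**What to change.** Add a short procedural paragraph to Data collection, or to Randomization and allocation concealment, with these elements:

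1. At each centre, the therapist who did not treat the participant takes the 4-, 18- and 24-month measurements. That therapist is not told the allocation where this is feasible.
2. Orthoses and diary are kept out of sight during the assessment, and the participant is asked not to reveal the group, as is already planned for the surgeon.
3. All measurements are completed before any adjustment of exercises or orthoses. The current text mentions them in this order but does not require it.
4. The check of questionnaires for missing data is done by someone other than the treating therapist. A study assistant is one option, since the article already uses one to check data entry.
5. Where a centre cannot do this, the eight outcomes are reported as assessed unblinded, and the pain ratings after grip and pinch are flagged with them.

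The cost is the paragraph and the scheduling, since both therapists must be available on assessment days. Masking will be incomplete because both therapists are providers and participants may let their group slip. No outcome, sample size or analysis model changes.

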### Randomization and allocation concealment

The randomization schedule will be prepared by a biostatistician making a computer-generated, randomized list with a block size of 10.

A secretary will prepare sealed, opaque envelopes containing the patient’s assignment to either the occupational therapy or the control group. The envelopes will be stored in a locked closet at each centre and may be opened by the participant after baseline assessments and information about HOA are completed.

In this trial, participants and therapists delivering the intervention are aware of the treatment assigned. To achieve blinding in the surgical consultation, participants will be asked not to inform the surgeon about their group allocation during the consultation. Moreover, the statistician who will perform the main statistical analyses will be blinded to group allocation.

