### Sample size calculations

The primary outcome will be differences between the groups in the number of participants who have received surgical treatment after 2 years. Calculation of sample size is based on the assumptions that at least 70% of those who are currently deemed eligible for surgery will undergo operations, and that the number of operations in the intervention group will be equal to or less than that of the control group (one-sided calculation). To be able to detect a difference of 20% in surgery rate between the groups, with a power of 80%, a significance level of 0.05 and a 20% dropout rate, a total of 180 participants (90 in each group) will be needed.

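### One constant block size of 10, with open allocation and envelopes held at the centres, could make up to about one allocation in six certain in advance; varied, undisclosed blocks would avoid this cheaply

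*Protocol article*

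**What the plan says.** The section Randomization and allocation concealment has a biostatistician prepare "a computer-generated, randomized list with a block size of 10". On concealment it says: "A secretary will prepare sealed, opaque envelopes containing the patient’s assignment". On custody: "The envelopes will be stored in a locked closet at each centre and may be opened by the participant after baseline assessments". The same section states that "participants and therapists delivering the intervention are aware of the treatment assigned".

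The Participants section gives recruitment at each centre to one role. The local coordinator sees the referral lists, telephones those who agree and books the baseline visit. On arrival, "the local project coordinator will screen the potential participant for eligibility before discussing the study with participants and obtaining their written informed consent". All of this comes before randomization.

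Two further details bear on who might know earlier allocations, both under Data collection. The two arms are contacted differently at 2 weeks: a telephone interview for controls, a second consultation for the intervention group. Local coordinators are also among those with access to the data file.

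The article does not say that block sizes vary, that the size is kept from the centres, that lists are separate by centre, or that coordinators are kept unaware of earlier allocations.

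**The concern.** Sealed, opaque envelopes hide a single assignment. They do not stop someone from working out the next one from those already opened. With a constant block of 10 split 5 and 5, the remaining assignments are fixed as soon as one arm has been used five times. An observer needs only the block size, the block boundaries and a tally.

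The coordinator who screens and seeks consent is the person for whom such knowledge would matter. One exclusion, other disease or injury that may impair hand function, leaves room for judgement, and the consent talk can be more or less encouraging. The primary outcome is receipt of surgery within 2 years, which plausibly depends on how much the patient wants it. If foreknowledge affected who entered, even unintentionally, the arms could differ at entry. Neither intention-to-treat analysis nor a blinded statistician repairs that.

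**Working it through.** **Inputs.** Block size 10 (Randomization and allocation concealment). Allocation 1:1, hence 5 + 5 per block; this is inferred from Sample size calculations: "a total of 180 participants (90 in each group) will be needed". Three centres (Study design and setting). The article gives no predictability figure of its own to reproduce, and the total of 180 enters only as a multiplier.

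**Certain allocations in a fixed block of 10.** There are C(10,5) = 252 equally likely orderings. The last k allocations are certain, and no more than k, when the block ends in a run of exactly k of one arm. That happens in 2 × C(9 − k, 4) orderings:

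| k certain | orderings | share |
|---|---|---|
| 1 | 140 | 55.6% |
| 2 | 70 | 27.8% |
| 3 | 30 | 11.9% |
| 4 | 10 | 4.0% |
| 5 | 2 | 0.8% |

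The mean is (140×1 + 70×2 + 30×3 + 10×4 + 2×5)/252 = 420/252 = 1.667 per block. This agrees with the closed form 2m/(m + 1) with m = 5, that is 10/6. As a share it is 16.7%. Over 180/10 = 18 complete blocks, 18 × 1.667 = 30 allocations. Every complete block has at least one certain allocation, and 112/252 = 44% have two or more.

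**Best guess.** Always guessing the arm with more places left, and counting a tie as one half, gives m + (4^m / C(2m,m) − 1)/2 correct guesses per block. With m = 5: 5 + (1024/252 − 1)/2 = 5 + 1.53 = 6.53 of 10, or 65.3%, against 50% by chance.

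**If the list is not organised by centre.** In a simulation of one list shared by three equal centres, each centre saw only its own allocations but knew where blocks began. The certain share was about 0.07%. The range across readings of the article is therefore roughly 0 to 16.7%.

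**Alternatives.** The next simulation used 60 allocations per centre (180/3, assuming equal centres). The observer knows the set of possible block sizes but not which one applies:

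| Block sizes | Certain in advance | Best guess right |
|---|---|---|
| fixed 10 | 16.6% | 65% |
| 4, 6 | 5.5% | 69% |
| 4, 6, 8 | 2.3% | 68% |
| 6, 8, 10 | 1.6% | 66% |
| 8, 10, 12 | 1.3% | 65% |

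Varying the size removes nearly all the certainty. Keeping the sizes around 10 avoids the rise in guessing that small blocks bring.

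**The case against.** A reader might infer that local staff do know one allocation in six. The article does not support that, because the figure needs three conditions it does not state:

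- **Blocks within centre.** The article speaks of one list and does not mention stratification. Envelopes stored at each centre make whole blocks per centre the natural reading, but not a stated one.
- **Coordinators who track allocations.** Only participants and treating therapists are named as aware. Whether a coordinator is also a treating therapist is not said, nor whether the data file shows the arm.
- **Block size known during recruitment.** Registration was in February 2013 and the article cites software dated 2016. Recruitment dates are not given, so publication may not have reached centres while they were enrolling.

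A reader might also infer that the primary analysis ignores motivation for surgery. The article names the model without listing covariates, and a covariate list is commonly left to an analysis plan. Silence here is not evidence of omission, and motivation is recorded at baseline.

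There are real safeguards. Patients first respond to mailed information, exclusions are few, screening, consent and baseline assessment all precede opening, and the participant may open the envelope. Ten is also less predictable than fixed blocks of 4, 6 or 8 (33%, 25% and 20% certain).

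All of this stands, and it makes the size conditional. It does not remove the mechanism: the safeguards do not prevent deduction from earlier allocations, and eligibility and consent are the steps at which foreknowledge would act.

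**Conclusion.** The point holds as a conditional, avoidable weakness. One in six (1.67 per 10, an expected 30 or so of 180) is a ceiling. It applies if blocks run within centre, local staff know the size of 10, and they follow earlier allocations. Under those conditions the best guess is right about 65% of the time. With a list shared across centres, the certain share is close to zero. Nothing in the article shows that anyone predicted or steered an allocation, and the size of any resulting bias cannot be calculated from it. This is a low-priority improvement, worth making because it costs little.

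**What to change.** Prepare a separate list for each centre with randomly varied block sizes, for example 8, 10 and 12. Only the biostatistician should know the sizes, and they should not be disclosed until recruitment ends. If enrolment is under way, replace the unopened envelopes. Certain predictions then fall to about 1 to 2%, the guess rate stays at about 65%, and the arms are kept close to balance within each centre. The gain is confined to certain predictions, since ordinary guessing is no harder than before. The cost is a new list and new envelopes; the sample size does not change.

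If enrolment has closed, report whether lists were separate by centre and whether coordinators knew the block size and earlier allocations.
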